**Data collection process**

*Sample size*

Qualitative research

The actual sample size for the qualitative element of the study is unknown at the outset**.** The sample size will be determined when the “point of saturation” is reached (this is the point at which no new information emerges from each group of respondents). However, indicative figures for the qualitative component are 10 – 20 key informants, 20 semi-structured interviews, and 20 in-depth interviews and twenty-four focus group discussions (six for each respondent category).

Quantitative research

The sample size for the quantitative element of this study needs to provide sufficient power to detect clinically important effect sizes for both TB and HIV. The statistical analysis will thus involve multiple comparisons. The exact number of comparisons of primary interest will be kept to a minimum – but to ensure multiple comparison issues are accounted for, all of the sample size / power calculations detailed below are based on an alpha level of 1% rather than the conventional 5% level.

- - - - 1. TB

*Primary outcome measure*: number of TB patients starting treatment - the expected proportion of smear positive cases starting treatment in the control group is estimated to be 55% - an increase in this proportion to 70% in the intervention group will be considered clinically significant.

WHO estimates that Malawi is detecting less than 50% of smear-positive TB cases nation-wide (the international case detection target is 70%). Based on secondary data collected to date:

- the current catchment population of the Lilongwe District rural health centres in the two study clusters is approximately 1.1 million
- the total number of TB cases registered in these rural health centres for which data is available was 936, of which 329 were smear positives and the remaining 607 were smear negative and other forms of TB.

Thus, assuming that actual TB cases are not rising in the community year on year, the expected number of smear positive TB cases registering for treatment in each study group over a one year period would be (329 / 2 =) 165, with at least as many smear negatives and other forms of TB. As this constitutes 55% of all smear positive TB cases, the actual number of smear positive TB cases occurring in each study group will be (165 / 0.55 =) 300. This will provide 87.5% power to detect an increase in the number of smear positive TB cases registering for treatment from 165 (55%) in the control group to 210 (70%) in the intervention group. Given that 41% of the TB cases were smear positive (WHO, 2009), then 512 TB cases (all forms of TB) were expected to start TB treatment at the end of the intervention in the intervention arm.

- - - - 1. HIV

*Primary outcome measure*: number of HIV-infected patients starting ART – the expected proportion of HIV-infected patients starting ART in this region of Malawi is currently estimated to be 15% - an increase in this proportion to 18% (a 20% proportional increase) in the intervention group would be considered clinically significant.

The population of Malawi is approximately 11 million, of which (approximately) 1.1 million (10%) live in the rural areas of Lilongwe. Estimates taken from Malawi’s 5 year ART Scale-Up plan indicate that 85,000 new patients become eligible for ART each year across the country, so 8,500 new patients become eligible for ART in the rural areas of Lilongwe. Data collected by the REACH Trust indicate that the ART programme starts 1,300 people on treatment in the Lilongwe rural health facilities per year, a treatment initiation rate of (1300 / 8500 =) 15%. Thus, the number of new patients becoming eligible for ART in each of the two study groups will be 4,250. This will provide 86.9% power to detect a 20% increase in the proportion of eligible patients starting ART (in absolute terms, from 15% in the control group to 18% in the intervention group).

It is hoped that the intervention will have a much greater impact on the primary outcome measure, increasing the proportion of eligible patients starting ART in the intervention group well towards the national target figure of 50%.

With a decision to use six large clusters with at least 166,000 population to minimise pollution of the intervention, a proper sample size calculation using simulations will be implemented to guide the analysis plan. The simulation studies will be carried out before the analysis of the study.

*Data collection tools*

Data collection tools for primary and secondary outcome measures

Prior and subsequent to the intervention, the chronic cough registers, TB treatment registers, HTC and ARV Treatment Registers from health facilities in the whole of Lilongwe District (rural and urban) will be audited for patient numbers by health centre catchment area. These data will form the basis for the trial analysis. Place of residence data are crucially important in this study, so that the study staff can locate patients to traditional authorities and health centre catchment areas that are identifiable within either the intervention or the control area. The study staff will, therefore, conduct initial training and continuing quality assurance checks on these registers throughout the study.

Data collection tools for health economic evaluation

A questionnaire survey will be carried out on a random sample of 166 rural new smear positive TB patients (83 at each site) who have registered for treatment (or both) and 200 rural patients who have recently (within last 2 months) registered for ART at the beginning of the intervention and at the end of the trial period. A patient who has both started treatment for smear positive TB and who is registered for ART will count for both samples, therefore the total sample size may be less than 366. These surveys will capture HIV and TB patients’ pathways to care and collect data on individuals’ household assets and on health-seeking experiences around current symptoms, identifying where and why care was sought (appendix 4). Using a cost-effectiveness check-list data will be collected on staff, consumables, transport and other costs incurred by the health service in this intervention.

Data collection for process evaluation

Throughout the duration of the project, detailed monthly reports will be compiled and all minutes will be recorded. All individuals and organisations involved, their roles and their processes of engagement will be documented. Key informant interviews. Semi-structured interviews and in-depth interviews will also be done.

*Data analysis*

Qualitative data will be transcribed verbatim. The transcribed data will be saved as rich text file (RTF) format which will be imported in MAXQDA. It will be organised according to themes for analysis.

The quantitative data will be collected and stored using pre-prepared Excel, Access and/or EpiInfo software databases. The characteristic of the control and intervention groups will initially be summarised and compared using standard univariate statistical methods (Fisher exact test and Student t-test/Mann-Whitney U-tests for categorical and continuous measures respectively). Effect sizes for the primary and main secondary measures will be summarised using incidence rate ratios with their 95% confidence intervals. Poisson regression methods will be used to investigate in greater detail the factors influencing the two primary outcome measures, and to adjust the effect estimates for confounding factors. The analyses will be conducted using the SPSS and Stata statistical packages at the REACH Trust, with supervision and advice as necessary provided by [name] (Senior Lecturer in Medical Statistics, Liverpool School of Tropical Medicine).

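### The stated powers of 87.5% (smear-positive TB) and 86.9% (ART) come from two-proportion tests on denominators the trial never observes; the planned analysis compares register counts, for which 165 v 210 gives about 40% before clustering

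*Protocol*

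**What the plan says.** All of this is in the Protocol, under Data collection process.

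- **Outcome.** The TB primary outcome is the "number of TB patients starting treatment". The HIV primary outcome is likewise a number, of HIV-infected patients starting ART.
- **Power, TB.** The section states that "the actual number of smear positive TB cases occurring in each study group will be (165 / 0.55 =) 300". It continues: "This will provide 87.5% power to detect an increase in the number of smear positive TB cases registering for treatment", namely "from 165 (55%) in the control group to 210 (70%) in the intervention group". It then converts the 210 to 512 expected starts for all forms of TB in the intervention arm, using a smear-positive share of 41%.
- **Power, HIV.** It states that "the number of new patients becoming eligible for ART in each of the two study groups will be 4,250" and gives 86.9% power for 15% v 18%.
- **Alpha.** All the calculations are "based on an alpha level of 1% rather than the conventional 5% level". Sidedness is not stated.
- **Data.** Chronic cough, TB treatment, HTC and ARV registers "will be audited for patient numbers by health centre catchment area".
- **Analysis.** "Effect sizes for the primary and main secondary measures will be summarised using incidence rate ratios with their 95% confidence intervals". Poisson regression is named for the two primary outcomes.
- **Later work.** After the power calculations, the section says that a proper, simulation-based sample size calculation will be done before the analysis, because six large clusters were chosen. It gives no revised figure.

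**The concern.** The power calculation and the planned analysis are different comparisons. A two-proportion test needs to know, in each arm, how many people had smear-positive TB or became eligible for ART, including those who never reached a facility. The registers record only people who did reach one. The 300 is obtained by dividing the register count by an assumed proportion, and the 4,250 by scaling down a national planning figure. The analysis behind 87.5% therefore cannot be run on the data described.

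The substitution also affects precision. Treating 300 as fixed gives the control count a variance of 165 × 0.45 = 74. If the underlying case total varies as well, the number of starts behaves as a Poisson count with variance 165. The binomial model removes more than half of the variance that the rate-ratio analysis carries.

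At stake is how a null result would be read. A smear-positive comparison reported as having 87.5% power would be taken as good evidence against a worthwhile effect, when the count comparison had far less chance of detecting it.

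**Working it through.** **Inputs (Protocol, Data collection process).** Control 165 (329/2, rounded) and intervention 210 smear-positive registrations; 300 per arm; 55% v 70%. ART: 4,250 per arm, 15% v 18%, that is 637.5 v 765 starts. Alpha 0.01, z = 2.576. Two-sided testing is inferred because, with a continuity correction, it reproduces both stated powers.

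**1. Reproduce the stated powers.**
Power = Φ{[|p2 − p1| − 1/n − 2.576·√(2p̄(1−p̄)/n)] / √([p1(1−p1) + p2(1−p2)]/n)}

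- TB: n = 300, p̄ = 0.625. (0.15 − 0.0033 − 2.576 × 0.0395)/0.0391 = 1.15, so 87.46%. Stated: 87.5%.
- ART: n = 4,250, p̄ = 0.165. (0.03 − 0.0002 − 2.576 × 0.00805)/0.00805 = 1.12, so 86.90%. Stated: 86.9%.

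Without the continuity correction TB gives 89.1%. The arithmetic is right for two proportions.

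**2. Power for the planned comparison: two Poisson counts, equal person-time, no clustering.**
Power = Φ{ln(m2/m1)/√(1/m1 + 1/m2) − z}

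| Comparison | Rate ratio | ln ratio | SE | z | Power, 1% | Power, 5% |
|---|---|---|---|---|---|---|
| Smear-positive, 165 v 210 | 1.27 | 0.241 | 0.104 | 2.32 | 39.8% | 64.0% |
| ART, 637.5 v 765 | 1.20 | 0.182 | 0.0536 | 3.40 | 79.5% | 92.5% |

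For TB at 1%, a test on the difference gives 40.1%, a square-root transform 40.2%, and simulation of 400,000 Poisson pairs 39.7%. About 430 control registrations would be needed for 87.5% at the same ratio.

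**3. Why TB loses more than ART.** The ratio of Poisson to binomial variance on the log scale is:

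- TB: (1/165 + 1/210)/(0.45/165 + 0.30/210) = 2.60
- ART: (1/637.5 + 1/765)/(0.85/637.5 + 0.82/765) = 1.20

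**4. Grant that exactly 300 cases occur per arm.** The Poisson analysis does not use that number. Simulating binomial counts out of 300 and applying the Poisson test gives about 33% power at 1%, so 87.5% is not recovered.

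**5. Read the outcome as all forms of TB.**

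- Intervention 512 as stated; control 165/0.41 = 402 (derived here). z = 3.63, so 85.4% at 1%.
- From the registered total: control 936/2 = 468; intervention 468 × 210/165 = 596. z = 3.91, so 91.0% at 1%.

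The two differ because 329/936 = 35% of registered cases were smear-positive, against the 41% used for the 512.

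**6. Clustering, for scale only.** The Protocol gives no between-cluster variation. Assume a coefficient of variation k and three clusters per arm, so SE² = 1/165 + 1/210 + 2k²/3. At 1%, smear-positive power is 34% for k = 0.05, 23% for 0.10, 14% for 0.15 and 6% for 0.25, by normal approximation. A t-test on 4 degrees of freedom gives less.

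**The case against.** **The primary outcome is not smear-positive TB.** As worded it is all TB patients starting treatment, and the section carries its target through to 512 for all forms. On that reading the count comparison has about 85% to 91% power, close to the stated figure. This stands, and it rules out saying that the planned analysis of the named TB outcome has only 40% power. It does not rescue the 87.5%, which is expressly about smear-positive registrations; no power is stated for all forms.

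**The Protocol already treats these figures as provisional.** It promises a proper simulation-based calculation. That is a fair qualification, but the reason given is the choice of six large clusters. The promise does not mention the difference between proportions and counts, and it does not withdraw 87.5% or 86.9%, which remain the only powers stated.

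**40% is no better a description of this trial.** A reader might infer that 40% and 79.5% are the trial's true powers, or upper limits on them. The documents do not support that. Both figures ignore the six clusters. The 329 covers only rural centres with available data, whereas outcomes will come from registers across the whole district, so actual counts may exceed 165. Whether data after the first 12 months enter the comparison is not stated. Pair-matching and baseline data could recover some of what clustering costs.

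**The ART gap is small.** Agreed: about 7 points, leaving roughly 80% at a strict alpha. On its own it would be a minor correction.

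**Conclusion.** The concern holds as a mismatch between the power model and the planned outcome and analysis. It is not an arithmetic error: both stated powers reproduce exactly. They belong to tests on denominators that no described data source supplies.

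For the smear-positive comparison, the corresponding count-based power is about 40% at two-sided 1%, or 64% at the 5% level implied by the planned 95% intervals, against 87.5% stated. For ART it is about 80% at 1% against 86.9%. These figures assume Poisson variation, equal person-time in the two arms, the Protocol's own expected counts and no between-cluster variation.

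The 40% applies to smear-positive registrations only. For all forms of TB the same method gives about 85% to 91%, so TB power depends heavily on which count is primary, and the text does not settle that. None of these is the operative power of a six-cluster trial.

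**What to change.** In the sample size section:

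1. State whether smear-positive or all-forms TB starts are the primary TB outcome.
2. Express the targets as counts and rate ratios: 165 to 210 (1.27), or the all-forms equivalent, and 637.5 to 765 (1.20) for ART.
3. Withdraw 87.5% and 86.9% as the power of the planned analysis. Report the count-based figures instead, labelled as a two-arm count comparison with no clustering.
4. Have the promised simulation generate counts within the six clusters, and take the operative power from it.
5. Keep 55% to 70% and 15% to 18% as background only, since the trial cannot estimate them.

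The cost is one decision on the outcome and the rewording of two paragraphs; the simulation is already promised. The stated power becomes less favourable, markedly so if smear-positive starts are primary.

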**Project site**

The project will be implemented in rural parts of Lilongwe district. Ideally, the study region would be divided into “clusters”, each consisting of geographically delineated area (defined by a combination of at least 2 traditional authorities). The clusters would then be randomised to either receive the intervention (Early intervention arm) or to act as a control, (Delayed intervention arm) using stratification methods to ensure that the two sets of clusters would be as similar as possible in terms of their poverty profile, population structure, health service coverage, and presence of significant number of at least one of the selected community-based health care providers (store-keepers, ante-natal care clinic and home-based care organisations).

The problem with this methodology is that people in the study clusters do not always attend their “local” health centre, so there would be considerable problems of “pollution” between the two study groups, in that people living in intervention clusters would attend control cluster health centres, and vice versa. While it would be technically relatively simple to identify the location of participants’ homes (and hence do an “intention-to-treat” analysis with individuals assessed according to their actual residence address rather than health centre attended), this would not eliminate the likelihood that some people resident in control clusters would be exposed to the intervention and some people resident in intervention clusters would not be exposed to it. The decision was thus taken to divide the rural parts of Lilongwe district into just six groups with large population sizes of at least 166,000. A random number will be generated in Excel to determine which clusters will receive the intervention early and which will ones will receive the intervention later. Thus, the six study clusters will equally be randomised to the Early intervention arm (to receive the intervention early in the first 12 months) and the Delayed intervention arm (to receive the intervention after 12 months). The 6 clusters will be pair-matched according to population sizes and their proximity to the urban areas.

Because the intervention is to be implemented at community level, allocation of the intervention will not be blinded to the communities and the research team implementing the intervention. However, allocation of TB and HIV cases to the clusters will be blinded.

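### The stated powers of 87.5% (TB) and 86.9% (ART) are for individually randomised patients, but the trial randomises six clusters, and no power is given for that design

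*Protocol*

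**What the plan says.** Under Project site, the protocol sets aside a design with many small clusters because of contamination and adopts six large ones, each with at least 166,000 people: "Thus, the six study clusters will equally be randomised to the Early intervention arm" or to the delayed arm. The six are pair-matched on population size and proximity to urban areas.

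The quantitative sample size section (Data collection process) sets the significance level for all its calculations, "based on an alpha level of 1% rather than the conventional 5% level". For TB, "the expected proportion of smear positive cases starting treatment in the control group is estimated to be 55" per cent, and "an increase in this proportion to 70% in the intervention group will be considered clinically significant". With 300 smear-positive cases per group, it concludes: "This will provide 87.5% power to detect an increase in the number of smear positive TB cases registering for treatment from 165 (55", rising to 210 (70%). For ART, with 4,250 newly eligible patients per group and 15% v 18%: "This will provide 86.9% power to detect a 20% increase in the proportion of eligible patients starting ART".

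No number of clusters, intracluster correlation, between-cluster variation or design effect enters either calculation. The TB paragraph still refers to "rural health centres in the two study clusters is approximately 1.1 million", and Project indicators also speaks of both clusters. The section's last paragraph says that, because six large clusters are now used, a proper calculation by simulation will follow to guide the analysis plan. On timing it says only: "The simulation studies will be carried out before the analysis of the study".

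**The concern.** Power depends on the unit that is randomised. With three clusters per arm, true differences in treatment initiation between areas add to the sampling error of the arm comparison, and more patients per cluster do not remove them. Six clusters also leave very few degrees of freedom for estimating that variation. A power computed from independent patients leaves out both, so it overstates what this design can do.

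The two figures are the only quantitative statement of power for the two primary outcomes. If they stand, a non-significant result for an effect near the planned size could be read against a power of about 87% and taken as evidence of no effect, in a project meant to inform policy. The pending simulation would correct this, but nothing requires it before the intervention begins or before outcomes accrue.

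**Working it through.** **Step 1: reproduce the stated figures.** Inputs from the sample size section: alpha 0.01 (two-sided is the version that reproduces); TB p1 = 0.55, p2 = 0.70, n = 300 per group; ART p1 = 0.15, p2 = 0.18, n = 4,250 per group.

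Power = Φ[(|p2 − p1| − 1/n − 2.576 × SE0) / SE1], where SE0 = √(2p̄(1 − p̄)/n), p̄ is the mean of p1 and p2, and SE1 = √([p1(1 − p1) + p2(1 − p2)]/n).

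- TB: (0.14667 − 2.576 × 0.03953)/0.03905 = 1.148, so power is 87.46% (stated 87.5%).
- ART: (0.029765 − 2.576 × 0.008052)/0.008045 = 1.122, so power is 86.90% (stated 86.9%).

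Without the continuity correction the results are 89.1% and 87.5%. One-sided tests, or alpha 5%, do not reproduce the stated figures. The figures are therefore those of independent individuals with no allowance for clustering.

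**Step 2: add between-cluster variation only.** Keep the plan's proportions and denominators, with 3 clusters per arm. Let k be the coefficient of variation of the true cluster proportions. The documents give no value, so a range is assumed. No gain is credited to matching or baseline data.

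V = [p1(1 − p1) + p2(1 − p2)]/n + k²(p1² + p2²)/3; δ = (p2 − p1)/√V; power = Φ(δ − 2.576), without continuity correction.

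Example, k = 0.10:
- TB: V = 0.001525 + 0.01 × 0.7925/3 = 0.004167; √V = 0.06455; δ = 0.15/0.06455 = 2.324; power = Φ(−0.252) = 40%.
- ART: V = 0.00006473 + 0.01 × 0.0549/3 = 0.0002477; √V = 0.01574; δ = 0.03/0.01574 = 1.906; power = Φ(−0.670) = 25%.

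**Step 3: add the degrees of freedom of six clusters.** Same δ, but a cluster-level t-test on 2 × (3 − 1) = 4 df (critical value 4.604 at two-sided 1%), with power from the non-central t distribution.

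| k (assumed) | Step 2, normal critical value: TB / ART | Step 3, t on 4 df: TB / ART |
|---|---|---|
| 0 | 90% / 88% | 41% / 39% |
| 0.05 | 74% / 61% | 28% / 22% |
| 0.10 | 40% / 25% | 14% / 9% |
| 0.25 | 7% / 4% | 3% / 2% |

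Reading down a column shows the effect of between-cluster variation; reading across shows the effect of few clusters. A paired analysis on 2 df, with no credit for matching, gives 15%/14% even at k = 0.

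**Step 4: how far this depends on the strict test and alpha.** At alpha 5% on 4 df, power for TB/ART is 82%/79% at k = 0 and 43%/31% at k = 0.10. With a simple design effect, 1 + (m − 1) × ICC with m = n/3 patients per cluster, and normal critical values at 1%, an ICC of 0.001 gives 86% for TB and 43% for ART; an ICC of 0.01 gives 55% and 5%.

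**The case against.** The strongest reply is that the protocol discloses the problem itself. Directly after the two calculations it says that six clusters call for a proper calculation, so the figures are provisional, and the result may sit in an analysis plan not shown here. That stands as far as it goes. A reader might infer that the sponsor believes it has about 87% power for this design; the last paragraph of the section does not support that. It does not cure the point either, since the figures are neither withdrawn nor labelled and no other figure is given.

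A reader might also infer that the simulation is planned for after the outcome data are in, so that the analysis could follow the results. The text does not say so. It sets a latest date and does not exclude an early run. What can be said is that no date before the intervention is fixed.

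The steepest losses come from a cluster-level t-test on 4 df at 1%, which the protocol does not name; its Data analysis section plans Poisson regression. This is fair, and it is why Steps 2 and 3 are kept apart. Matching and baseline data could recover some power, though the protocol quantifies neither and pairing costs degrees of freedom. Nothing in the documents supports the upper end of the range for k.

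Finally, it is tempting to call any null result uninformative. That holds for the planned minimum effects only. The protocol hopes ART initiation will move well towards 50%. Under the Step 3 model, 15% to 50% has over 99% power at k = 0.10 and about 58% at k = 0.25.

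**Conclusion.** The point holds. The arithmetic behind 87.5% and 86.9% is right for individually randomised patients, but those are not the powers of a trial that randomises three clusters per arm. The direction is certain: any positive between-cluster variance lowers power relative to the same calculation without it.

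The size rests on an assumed k, on the plan's own proportions and denominators, and on no credit for matching or baseline data. For k between 0.05 and 0.25, TB/ART power for the planned minimum effects at alpha 1% runs from 74%/61% down to 7%/4% when only between-cluster variation is counted. It runs from 28%/22% down to 3%/2% when the 4 degrees of freedom are counted too. If clustering is very weak and normal critical values are used, TB power could stay close to the stated figure (86% at an ICC of 0.001), but ART power would not (43%).

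The acknowledgement in the protocol limits the criticism to three things: the figures stand unlabelled, no cluster-based power replaces them, and the simulation has no date before the intervention.

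**What to change.** - Withdraw 87.5% and 86.9%, or label them as individual-level figures that do not apply to the six-cluster design.
- Run the simulation before the intervention starts, with six clusters, the actual analysis model, and a range of k informed by the pre-intervention register audit already planned. Use a range, because six clusters estimate k imprecisely.
- State the resulting power and the detectable effect for each primary outcome.
- Correct the reference to two study clusters in the TB paragraph to six clusters in two arms, and align the similar wording in Project indicators.

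The cost is protocol wording and some computation on register data that the project plans to collect anyway. No extra patients are needed. The downside is that the stated power becomes much less favourable.
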